## Abstract

Sedentariness of patients affected by end-stage kidney disease (ESKD) expose them to high risk of unfavorable clinical outcomes. Exercise training is effective in improving physical function, quality of life (QoL) and long-term outcomes. However, the existing barriers related to patients, programs and dialysis staff limit patient participation and call for new strategies. This pragmatic nonrandomized trial will test the impact on ESKD population of an intervention proposed by an exercise facilitator regularly present in a dialysis center. The patient will be free to choose among three-month walking and/or resistance low-intensity training programs: (a) guided physical activity increase; (b) home-based exercise; (c) in-hospital (pre/post dialysis) supervised exercise; (d) performance assessment only. The first phase will define feasibility and the characteristics and preference of responders. The second phase will evaluate safety and patients’ adherence. Outcome measures will be collected at baseline, after three-month and at six-month follow-up. They will include: aerobic capacity, QoL, gait speed, strength, depression and long-term clinical outcomes (hospitalization and mortality). The trial was approved by the Area-Vasta Emilia-Romagna Centro Ethics Committee with approval number 48/2019. Written informed consent will be obtained from all participants. The results of the study will be presented in international congresses, published in peer-reviewed journals and communicated to the patient community. Registration details: Clinicaltrials.gov NCT04282616 [Registered:24/02/2020].

## 1. Introduction

Chronic kidney disease affects 8–16% of the population worldwide [1]. This population tends to have a progressive decrease in physical activity, cardiorespiratory fitness and muscle mass due to the combined effects of uremia and physical inactivity [2]. Low physical activity levels are associated with the worst clinical outcomes in terms of both mortality and hospitalizations, especially in end-stage kidney disease (ESKD) [3,4,5]. In addition, impaired physical performance is related to an increased risk of falls, deconditioning, sarcopenia and all-cause mortality [6,7,8,9].

The guidelines recommend that patients with ESKD be counseled and regularly encouraged by nephrologists and dialysis staff to increase their level of physical activity [10,11]. Purposely, “intra or inter-dialytic” exercise programs or structured home-based exercise programs have been proposed [12,13,14]. Recently, those types of training programs were compared in a literature review [3], in which the authors concluded that inherent advantages and concerns were present with both approaches. Indeed, despite evidence of the beneficial effects of exercise on physical fitness, mobility, health-related quality of life (QoL) and clinical outcomes in all CKD patients [2,12,15], exercise programs of any kind are exceedingly rare in nephrology units [16,17]. Moreover, participation rates in the existing programs are low, with only 6.9% of patients meeting the recommended physical activity levels [6], therefore physical inactivity remaining a hallmark of the disease [1,3].

Several authors suggest that to address these issues, new approaches to implementing exercise in dialysis patients should be considered, particularly those that focus on simplifying exercise prescription [3,4]. In particular, the authors emphasized the failure of traditional one-size-fits-all program prescriptions due to the heterogeneity of the ESKD population [3,4] and recommended the design of individualized interventions to allow patients to select the types of activities in which they engage with more autonomy [3].

To fulfill these requirements in the ESKD population, several physical, psychological and environmental barriers that are still present need to be overcome. First, the identification of sustainable programs with good adherence is a priority because of these barriers [18,19,20]. Moreover, a proactive dialysis staff attitude is another crucial issue [21,22]; unfortunately, physical activity and exercise management are not routinely addressed in the care of these patients [2]. Although motivators to exercise have been reported in other diseases [23], nurse-led disease management programs in patients on dialysis have been tested [24,25] but not for promoting physical activity.

This pragmatic trial aims to test the impact of the regular presence of an exercise facilitator in a dialysis center to promote physical activity in the ESKD population. The efficacy will be verified in terms of applicability and feasibility, and the preferred and most effective exercise pathways for the patients will be identified. Secondarily, the study aims to carry out exploratory analyses to evaluate the impact of different exercise interventions on the functional and clinical parameters of the patients.

## 2. Experimental Design and Methods

### 2.1. Trial Design

This protocol is reported following the Standard Protocol Items: Recommendations for Interventional Trials (SPIRIT) guidelines [26]. The study is a pragmatic feasibility nonrandomized implementation trial that also includes a qualitative research study.

### 2.2. Study Setting

The study will take place at the two dialysis venues of the Operative Unit of Nephrology and Dialysis located in two different locations: at the University Hospital of Cona, Ferrara and at Città della Salute, Ferrara. All the interventions scheduled, as well as the outcome measure assessment, will be performed in a purposely selected space inside each dialysis center. The study follows two different phases, as described below, to be completed within 3 years.

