## 3. Procedures

### 3.1. Phase 1

In this phase, the exercise facilitator (EF) will be set up in the dialysis center. He/she will be an experienced physiotherapist and/or qualified exercise specialist who will be active in the dialysis centers for a specified number of hours per day to counsel patients concerning their worries and answer questions concerning physical activity. The EF will be properly trained by the members of the Rehabilitation Medicine Unit at the University Hospital of Ferrara on the management of frail patients by having experience with severely disabled patients with different conditions before the beginning of the study.

Stakeholder involvement: The EF, in collaboration with the team members, will prepare the informative material for the project. Team members will arrange meetings with unit personnel and coordinators of patient groups to introduce the EF figure, to explain the aims of the project and to address doubts and questions.

After the baseline outcome assessment, the EF will propose one of the four interventions to the patients by means of a specifically designed brochure, which is explained in the following section.

Qualitative outcomes will be employed in the first phase (Table 1). The rate of patients providing consent compared to the number of eligible patients, as well as the rate of patients choosing each of the training options proposed, will be calculated to determine patients’ willingness to exercise and their preferences about training. The impact of the patients’ characteristics and other variables on the choice of the program will also be investigated.

### 3.2. Phase 2

The EF will ask each enrolled patient to select an intervention and thus enter into one of the following arms.

Unstructured physical activity (U-PA)

According to each patient’s baseline physical activity level previously measured, the EF will advise patients to start or increase their spontaneous activity by counseling them on total exercise time, mode, intensity and frequency as suggested by the guidelines [27,28] (Table 2). A log-book and a wearable physical activity monitor will be provided to each patient. The instruments have to be returned in the subsequent controls, to encourage adherence and objectively measure the exercise activities.

Structured home-based low-intensity exercise (S-HB-LI)

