According to each patient’s baseline physical activity level, a semipersonalized walking program will be provided. This program, derived from previous experience with ESKD patients [13,29] was also successfully tested in other fragile populations such as stroke survivors or multiple sclerosis patients [30,31,32]. The training program will be performed at home at a prescribed speed and it includes a 10-min session/day of intermittent walking (1- or 2-min work and 1-min seated rest). The speed which is converted into a walking cadence is increased weekly and it is controlled at home with the aid of a metronome (Table 2). Patients will be provided with a daily log containing the detailed exercise prescription and free lines to provide feedback on training execution and any possible related symptoms.

Structured supervised low-intensity exercise (S-SU-LI)

Patients will meet at a specified location (room or corridor) into the dialysis unit for the exercise program in groups of a maximum of four subjects. The thirty-minute training session will be scheduled on a 2- or 3-time/week pattern, and they will be performed immediately before or after the dialysis treatment or according to patients’ preferences and considering the postdialysis fatigue that affects this population [33].

Each session will include low-intensity walking exercises (similar to those for the structured home-based training) and resistance and power exercises with elastic bands and ankle/wrist weights. Each session will begin and end with a warm-up and cool-down period of stretching, respectively. The total duration of the session will be approximately 30 min. The training intensity will be set according to the patient’s baseline capacity and it will be weekly increase. The rate of perceived exertion will be always collected (Table 2).

Physical performance assessment only (PPA)

Patients choosing this option will not begin any exercise program, but they will perform the outcome measures session only. A switch to another treatment, periodically proposed by the EF, will be always possible.

Study design is presented in Figure 1.

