### 3.10. Statistical Analysis

In the first qualitative phase, descriptive statistics, chi-squared tests and mixed models of analysis will be employed. Regression analyses will be conducted to determine if different variables (e.g., distance from dialysis center and presence of a caregiver) might interfere with patients’ decisions. Furthermore, the physical activity level and physiological and psychological variables assessed at baseline will be considered independent variables in the regression models.

In the second phase, standard methods of analysis for clinical trials will be used. First, baseline comparisons of patient characteristics for each group will be compared for demographics and primary and secondary outcome measures. The data distribution will also be verified through a Shapiro–Wilk test. A two-way repeated measure analysis of variance will be used to compare differences in the primary and secondary outcomes. Within-group comparisons will be performed via paired Student’s t-tests or Wilcoxon tests, as appropriate. If a significantly different distribution between the baseline characteristics of the group is identified, a secondary analysis that employs multivariate modeling to adjust for these factors will be performed (e.g., linear mixed models for repeated-measures analyses with unbalanced design). Moreover, Kaplan–Meier analysis and Cox regression will be used to model incidence rates for long-term clinical outcomes (hospitalization rate and death). Finally, a post hoc power analysis will also be carried out to determine the clinical impact of the findings.

All analyses will be conducted using intention-to-treat. Missing values, though we will make any effort possible to reduce their incidence, will be treated using the multiple imputation procedure. Moreover, a per-protocol analysis to assess the stability of the study’s conclusions will also be performed. Properly gender-oriented analyses will be carried out for most of the outcomes. A *p* value of 0.05 will be considered statistically significant.

Statistical analysis will be performed with SPSS 21.0 (IBM, Armonk, NY, USA) and MedCalc statistical software (version 19.4.0 and following, MedCalc Software bvba, Ostend, Belgium).

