### 3.11. Data Monitoring and Interim Analysis

As this is a single-center study, a data monitoring committee will not be required. The research coordinator will be responsible for the interim analysis (in terms of recruitment and preliminary results) and for making the final decision to stop or conclude the trial.

The final dataset of the study will be completely available in a public repository.

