### 4.2. Trial Limitations

This trial presents several limitations, as it is a single-center nonrandomized study. Moreover, a typical during-dialysis treatment training option is not scheduled, despite the evidence in the literature [14,15]. However, we aim to test training solutions requiring minimal space and equipment that are implementable in most dialysis centers worldwide and not overtaxing of the personnel and the routine of a dialysis center. In addition, the study design will likely introduce a selection bias in the enrolled population, as conceivably fitter patients may opt for the walking or mixed training programs, while less fit patients may choose for the unstructured increase in physical activity; proper methods of analysis will be used to overcome the lack of randomization. These factors may limit the generalizability of the findings as well the possibly small sample size that will occur in case of limited participation of patients.

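### The main Phase 2 analysis has no venue term, and its only route to adjustment is a baseline significance test, so a difference between the two venues could pass as a program effect

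*Protocol article*

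**What the plan says.** All places are in the protocol article.

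- **Setting (2.2).** "The study will take place at the two dialysis venues of the Operative Unit of Nephrology and Dialysis located in two different locations". Interventions and outcome measurements "will be performed in a purposely selected space inside each dialysis center".
- **Facilitator and training space (3.1, 3.2).** The exercise facilitator is "active in the dialysis centers for a specified number of hours per day", with no split by venue. For the supervised option, "Patients will meet at a specified location (room or corridor) into the dialysis unit". Each patient selects the arm.
- **Phase 2 analysis (3.10).** "A two-way repeated measure analysis of variance will be used to compare differences in the primary and secondary outcomes". The two factors are not named; arm and time is the natural reading. Multivariate modeling, with linear mixed models as the example, is a secondary analysis. It is run if the groups differ significantly at baseline, and it adjusts for the factors that differ.
- **Phase 1 analysis (3.10).** Chi-squared tests, mixed models and regressions of patients' decisions are planned. The covariate list is open, and distance from the dialysis center is one example.
- **Center status (3.11, 4.2).** "As this is a single-center study, a data monitoring committee will not be required" and "This trial presents several limitations, as it is a single-center nonrandomized study".

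Venue is not named as a factor, covariate or reporting stratum anywhere.

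**The concern.** Arms are chosen, not assigned, so nothing in the design balances the venues across arms. The supervised option is the one most tied to place, since it depends on a room or corridor in the unit and on the facilitator being there. Its uptake could therefore differ between venues. If the venues also differ in how much patients' walking distance changes over three months, an arm-by-time contrast without a venue term attributes part of that difference to the program.

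This goes beyond one covariate missing from a list. The article fixes the unadjusted model as the main analysis and makes adjustment depend on a significance test. That is a poor rule for a self-selected design. A confounder does its damage according to the size of the imbalance and its link with outcome, not according to whether a test on small arms reaches 0.05. It is also unclear whether venue would count as a patient characteristic for the purpose of the trigger.

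At stake is the aim, stated in the introduction, of identifying the most effective exercise pathways. To a lesser degree the implementation result is affected too, since rates by venue would show whether the facilitator's presence worked at both places.

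**Working it through.** The plan gives no figure on venue, so there is none to reproduce. What follows shows how large the problem could be.

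**Inputs from the protocol (3.8, 3.10).** About 140 patients; 50% acceptance; target 88; significance level 0.05 (taken as two-sided).

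**Assumed inputs, not in the documents.** Equal arm sizes for step 1; the venue shares within arms; the venue difference in mean change in 6-minute walk distance; for step 3, 44 patients per venue and an SD of change of 50 to 70 m.

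**Step 1. Would the baseline trigger notice a venue imbalance?**
Arm size is 140 × 0.5 / 4 = 17.5, or 88 / 4 = 22.
For two arms of n patients with venue shares p1 and p2 (mean p̄):
SE0 = √[2p̄(1−p̄)/n], SE1 = √{[p1(1−p1) + p2(1−p2)]/n}, power = Φ[(|p1−p2| − 1.96·SE0)/SE1].

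- 60% v 40%, n = 17: SE0 = 0.1715, SE1 = 0.1680, so Φ[(0.20 − 0.336)/0.168] = Φ(−0.81) = 0.21.
- 60% v 40%, n = 22: SE0 = 0.1508, SE1 = 0.1477, so Φ[(0.20 − 0.295)/0.148] = Φ(−0.65) = 0.26.

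| Venue shares in two arms | Chance of being flagged (n = 17 to 22) |
|---|---|
| 60% v 40% | 21–26% |
| 70% v 30% | 66–78% |
| 80% v 20% | 97–99% |

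A four-arm chi-squared test (noncentral chi-squared, 3 df, 17.5 to 22 per arm) flags shares of 50/50/40/60% in 15–17% of cases and 50/50/30/70% in 49–59%. Only an extreme imbalance is caught reliably.

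**Step 2. Bias in an arm contrast without a venue term.**
Bias = (difference in venue share between arms) × (venue difference in mean change).

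| Share difference | 10 m | 20 m | 30 m | 40 m |
|---|---|---|---|---|
| 10 points | 1 | 2 | 3 | 4 |
| 20 points | 2 | 4 | 6 | 8 |
| 30 points | 3 | 6 | 9 | 12 |
| 40 points | 4 | 8 | 12 | 16 |

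The range is 1 to 16 m, and the bias is 0 if either difference is 0. The relevant venue difference is in change. A constant difference in level between venues cancels from the arm-by-time contrast.

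**Step 3. Effect on the false-positive rate, for one illustrative contrast (supervised arm versus all others).**
With 44 per venue and supervised uptake of 50% and 20%, the supervised arm has 22 + 8.8 = 30.8 patients and the rest 57.2. The share difference is 22/30.8 − 22/57.2 = 0.330. A venue difference of 15 to 30 m gives a bias of 4.9 to 9.9 m.
SE = SD × √(1/30.8 + 1/57.2) = 11.2 m (SD 50) to 15.6 m (SD 70).
With b = bias/SE, rate = Φ(−1.96 + b) + Φ(−1.96 − b).

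| Uptake at the two venues | Share difference | Bias | False-positive rate |
|---|---|---|---|
| 40% / 25% | 0.171 | 2.6–5.1 m | 5–7% |
| 50% / 20% | 0.330 | 4.9–9.9 m | 6–14% |
| 60% / 10% | 0.549 | 8.2–16.5 m | 8–31% |

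For mild differences in uptake the rate stays near nominal. It becomes serious only when uptake and change both differ markedly between venues.

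**The case against.** The strongest objection is that this is a missing covariate, and a journal article may leave its covariate list to the analysis plan. For Phase 1 that is largely right. The list is open, distance from the center covers part of the access question, and nothing excludes venue. It would be wrong to infer that the whole analysis rests on arm and time alone; that describes only the main Phase 2 ANOVA. For Phase 2 the objection fails, because the article itself fixes an unadjusted main model and a significance trigger.

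A second objection is that no venue effect is documented. This stands. Both venues belong to one unit, the supervised space is said to be specified, 3.6 sets one walkway length for the walk test, and assessors are blinded (3.7). Nothing says that facilitator hours, case-mix or care differ. A reader might infer that venue differences exist and will be mistaken for program effects; the documents support only that they could be.

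A third objection is that the single-center label is not an error. This also stands: two sites of one operative unit can fairly be called one center. The pooled responder rate is likewise a valid unit-level figure. If the venues had 40% and 60% consent and equal numbers of eligible patients, 50% would still be the correct rate for the unit.

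Finally, the introduction calls the comparisons of interventions exploratory, and 4.2 already concedes selection by fitness, which may well be the larger threat. This limits the weight of the point but does not argue against adjusting for a factor that is easily recorded.

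**Conclusion.** The point holds as a risk that the stated Phase 2 analysis leaves open, not as a demonstrated bias. Two venues, self-chosen arms, an unadjusted main model and a trigger with little power are all in the text. The trigger would miss a 60/40 venue imbalance between two arms about three times in four. The resulting bias in 6-minute walk change is roughly 1 to 16 m under the assumed venue shares and venue differences, and zero if venue is unrelated to either choice or change. These metre figures rest wholly on assumptions, since the documents give no venue split, no SD of change and no venue effect. The documents do not support a claim that the venues differ, that Phase 1 ignores covariates, or that calling the study single-center is a contradiction. The change is worth making because it is cheap and the present rule is weak.

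**What to change.** In section 3.10:

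1. **Phase 2.** Include venue and venue-by-time in the repeated-measures model for the primary and secondary outcomes, whatever any baseline test shows. The linear mixed model that 3.10 already names would serve. Venue-by-time is the term that removes venue confounding of change.
2. **Phase 1.** Include venue as a fixed factor in the regression of program choice, and in that of consent where the data on non-consenting patients allow.
3. **Reporting.** Give the consent rate and choice shares for each venue, with intervals, beside the pooled unit rate.

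The cost is a few lines of text. Phase 2 loses about three degrees of freedom (one for venue, two for venue-by-time over three assessments) and each Phase 1 regression loses one. Venue should be known for every patient. Per-venue rates will be imprecise at this sample size and should be presented as descriptive.

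This removes venue confounding only; self-selection by fitness (4.2) still needs its own handling. The single-center wording can stay. A log of facilitator hours per venue, and a rule for which venue peritoneal dialysis patients are counted under, would help interpretation but are optional.

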### 2.3. Participants

The study aims to recruit ESKD patients undergoing peritoneal or hemodialysis treatment.

Inclusion criteria: males and females patients aged ≥18 years; able to walk for at least 6 m; performing dialysis for at least 3 months in stable conditions; Mini Mental Status Examination score ≥18/30 sufficient to enable patients to give informed consent.

Exclusion criteria: uncorrected anemia (hemoglobin concentration <9 g/dL); acute infectious disease (C-reactive protein > 10 mg/L), severe cardio-respiratory (e.g., unstable angina; severe heart failure identified by New York Heart Association class III-IV), musculoskeletal or neurological conditions (e.g., lower limbs major amputation) inhibiting exercise training.

As this is an implementation feasibility trial, the exclusion criteria are kept at a minimum.

During the first meeting with potential participants, the study personnel will check patients’ interest in taking part in the study; if a positive response is provided, a screening visit to verify compliance with the inclusion criteria will be executed. Patients meeting the eligibility criteria will be given a letter explaining the study, as well as the consent form, and they will be encouraged to ask any questions. Within seven days, patients will be asked to return a signed copy of the consent form; if the patients have not yet decided, they will be given adequate time to consider their participation. According to the guidelines [26], the total number of screened subjects who are ineligible (and the reasons for their ineligibility) or not willing to participate in the study (along with the reasons and the main clinical characteristics, if provided) will be tracked.

Preparticipation screening with exercise testing will not be regularly scheduled due to the low intensity of the exercise program proposed, as it was designed for special populations [27].

For those who volunteer to participate, baseline outcome measurement sessions will be scheduled within two weeks. In this timespan, patients will be provided with a wrist fitness tracker to be worn continuously for 6 days, including at night and during resting periods. The number of daily steps, number of hours of sleep or rest and heart rate will be recorded.

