### 3.8. Sample Size

To the best of our knowledge, this is the first trial of this type exploring patient preferences about programs and comparing the outcomes for these programs. Therefore, a power calculation hypothesizing a better effect of one program compared to another could not be performed; in addition, the investigators do not assign the interventions, and they do not know a priori how many patients will select each training option.

Otherwise, we aim to recruit a sufficient number of participants to address the study’s implementation objectives. The Nephrology Unit at the University Hospital of Ferrara manages approximately 140 patients on dialysis. The entrance of new patients into dialysis service will be checked every 3 months. We will try to propose the programs to all eligible patients and hypothesize a 50% rate of acceptance, which might be progressively increased by word of mouth among patients.

According to a power calculation based on a theoretical responder rate of 50% and considering a margin of error equal to 5% and a confidence level of 90%, a total of 88 patients will be required to make the first qualitative phase of the study representative of the population.

To optimize recruitment, all members of the Nephrology Unit of the hospital will be informed about the trial during team meetings. Information on the study procedures will also be given to the CKD and ESKD support groups, which will share the study information through their newsletters and website.

The EF will be available daily in the dialysis room to encourage patient participation. Informative material will also be available in the Nephrology Unit wards.

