**Outcomes**					
*Phase 1*					
% Patients responders/eligible		X			
Physical and emotional status		X			
Exercise program choices		X			
Factors related to choices		X			
*Phase 2*					
Safety (adverse events, interruptions)			X		
Adherence (% sessions completed)			X		
6MWT (primary outcome)		X	X	X	
Gait speed, lower limbs strength, quality of life, depression, estimated capacity, fear of falling (secondary)		X	X	X	
Biochemical/laboratory markers		X	X	X	
Hospitalizations and mortality				X	X

Abbreviations: U-PA-I: unstructured physical activity increase; S-HB-LI: structured home-based low-intensity; S-SU-LI: structured supervised low-intensity; PPA: physical performance assessment; 6MWT: 6-min walk test.

**Table 2 mps-03-00083-t002:** The different interventions proposed to the patients by the exercise facilitator.

Program	U-PA-I			S-HB-LI			S-SU-LI			PPA Performance Assessment
	Unstructured Physical Activity Increase			Structured Home-Based Low Intensity			Structured Supervised Low Intensity			
*Setting*	Home			Home			Dialysis Center			-
*Frequency*	Daily			Daily			2- or 3-Time a Week			
*Baseline 6MWD (m)*	<200	201–400	>400	<200	201–400	>400	< 200	201–400	>400	-
*Program features*	Walking (mins) Intensity: moderate [27,28]			Walking: rest (min) × reps Speed (steps/min)			Walking * + strength leg extension/leg curl/shoulder abduction (reps × series − load)			
*Week 1*	5	10	15	1:1 × 6 − 60	1:1 × 8 − 60	1:1 × 8 − 72	3 × 2 – 0.5 kg	3 × 3 − 1 kg	3 × 3 – 1.5 kg	-
*2*	5	10	15	1:1 × 6 − 63	1:1 × 8 − 63	1:1 × 8 − 76	3 × 2 – 0.5 kg	3 × 3 − 1 kg	3 × 3 – 1.5 kg	
*3*	10	15	20	1:1 × 8 − 63	1:1 × 8 − 66	1:1 × 8 − 80	4 × 2 − 1 kg	4 × 3 − 1 kg	4 × 3 – 1.5 kg	
*4*	10	15	20	1:1 × 8 − 66	1:1 × 8 − 69	1:1 × 8 − 84	4 × 2 − 1 kg	4 × 3 − 1 kg	4 × 3 – 1.5 kg	
*5*	15	15	20	1:1 × 8 − 66	1:1 × 8 − 72	1:1 × 8 − 88	3 × 3 − 1 kg	4 × 3 – 1.5 kg	4 × 3 − 2 kg	
*6*	15	20	20	1:1 × 8 − 69	1:1 × 8 − 72	1:1 × 8 − 92	3 × 3 − 1 kg	4 × 3 – 1.5 kg	4 × 3 − 2 kg	
*7*	15	20	25	1:1 × 8 − 69	1:1 × 8 − 76	2:1 × 4 − 72	4 × 3 − 1 kg	4 × 4 – 1.5 kg	4 × 4 − 2 kg	
*8*	20	20	25	1:1 × 8 − 72	1:1 × 8 − 76	2:1 × 4 − 76	4 × 3 − 1 kg	4 × 4 – 1.5 kg	4 × 4 − 2 kg	
*9*	20	20	25	1:1 × 8 − 72	1:1 × 8 − 80	2:1 × 4 − 80	4 × 3 – 1.5 kg	4 × 4 − 2 kg	4 × 4 – 2.5 kg	
*10*	20	25	25	1:1 × 8 − 76	1:1 × 8 − 80	2:1 × 4 − 84	4 × 3 – 1.5 kg	4 × 4 − 2 kg	4 × 4 – 2.5 kg	
*11*	20	25	30	1:1 × 8 − 76	1:1 × 8 − 84	2:1 × 4 − 88	4 × 4 – 1.5 kg	5 × 4 − 2 kg	5 × 4 − 3 kg	

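### Eligibility is verified only in patients who have already voiced interest, so the only verified denominator for the Phase 1 responder rate is conditional on interest and can overstate uptake among all eligible patients

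*Protocol article*

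**What the plan says.** **Order of steps (section 2.3).** Study personnel ask about interest at a first meeting. Then "if a positive response is provided, a screening visit to verify compliance with the inclusion criteria will be executed". Patients found eligible receive the explanatory letter and the consent form.

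**Tracking (section 2.3).** The plan will record "the total number of screened subjects who are ineligible (and the reasons for their ineligibility) or not willing to participate in the study". Reasons and main clinical characteristics are added only where the patient supplies them.

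**Outcome definition.** Section 3.1 defines the rate as "The rate of patients providing consent compared to the number of eligible patients". Table 1 lists it as "Patients responders/eligible".

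**Companion rate and use.** Section 3.1 pairs the consent rate with a second one, "as well as the rate of patients choosing each of the training options proposed", and says that the two "will be calculated to determine patients’ willingness to exercise and their preferences about training".

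**Planning assumption (section 3.8).** "We will try to propose the programs to all eligible patients", with 50% acceptance assumed in a unit of about 140 dialysis patients. The sample size uses this 50%, a 5-point margin and 90% confidence.

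**Assessment-only option (PPA, section 3.2).** "Patients choosing this option will not begin any exercise program".

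**The concern.** The responder rate needs a count of eligible patients that does not depend on their answer. The written sequence does not produce one. A patient who says no at the first meeting gets no screening visit, so whether that patient was eligible is not established. The procedure yields a verified eligible count only among patients who said yes.

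This matters because the abstract gives Phase 1 the task of defining feasibility, and the sample size in section 3.8 is built on this proportion. A rate that is conditional on interest answers a different question: how many interested and eligible patients go on to sign. That would make the facilitator model look more acceptable than it is. Recruiting more patients would not remove the difference.

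**Working it through.** **Plan's own figure.** Section 3.8 states 88 patients for a 50% rate, 5-point margin and 90% confidence. The usual calculation is n0 = 1.645² × 0.5 × 0.5 / 0.05² = 270.6, then n = n0 / (1 + (n0 − 1)/N). With N = 140 this gives 92.5, so 93; with N = 130 it gives 88.0. The stated 88 is therefore not reproduced from 140 patients. That is a separate matter. Only the 50% and the 5-point margin are used below.

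**Passages side by side.**

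1. Section 2.3: interest, then eligibility check, then consent.
2. Section 3.1 and Table 1: consenters divided by eligible patients.
3. Section 3.8: the proposal goes to all eligible patients. This presupposes that eligibility is known before the proposal, which step 1 does not provide.
4. Section 3.1: the facilitator presents the four options after the baseline assessment, so to patients who have already consented.

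The tracking sentence does not close the gap. It speaks of screened subjects. Even if it is read to include first-meeting decliners, it records no eligibility status for them, so they could be counted but not placed among the eligible.

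**Direction.** Every consenter has passed through the interest step, so the numerator is the same under either denominator. Eligible patients who voiced interest are a subset of all eligible patients. The conditional rate therefore cannot be lower than true uptake.

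**Size.** Let t be true uptake among all eligible patients and s the share of eligible refusers who decline at the first meeting and so fall outside the verified denominator. Then

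measured rate = t / (1 − s(1 − t)).

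With t = 0.5 (the planning value) this is 0.5 / (1 − 0.5s). The documents give no value for s, so a range is assumed:

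| s (assumed) | measured rate | excess over 50% |
|---|---|---|
| 0 | 50.0% | 0 |
| 0.10 | 52.6% | 2.6 points |
| 0.25 | 57.1% | 7.1 points |
| 0.50 | 66.7% | 16.7 points |

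For example, take 100 eligible patients with 50 consenting and 50 refusing. If 25 of the refusers decline at the first meeting, the rate becomes 50/75 = 66.7%.

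**Threshold.** The excess passes the planned margin when 0.5 / (1 − 0.5s) > 0.55, that is 1 − 0.5s < 0.909, so s > 0.18.

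**Assessment-only patients.** Consent precedes the choice of option, so overall consent includes PPA. With 50% consent and an assumed 10% to 30% of consenters choosing PPA, the share of eligible patients choosing an active program is 0.5 × 0.90 = 45% down to 0.5 × 0.70 = 35%.

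**The case against.** The strongest reply is that the plan never says first-meeting decliners are left out. It says eligible patients without qualification, section 3.8 shows that all eligible patients are meant, and unwilling patients are to be tracked. Verifying may mean confirming a status already presumed from the records of a single unit. A condensed article may also leave the screening log to the full protocol.

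Part of this stands. The intended denominator is probably all eligible patients, and patients who decline after screening are counted. What does not stand is that the written steps deliver that denominator. No pre-screening from records is described, and the order of steps is stated in the article rather than left out of it.

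Two stronger readings are tempting and should not be drawn:

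- **That the rate omits refusers and is inflated by a known amount.** One could assume 112 eligible, 67 interested and 56 consenting, and compare 56/67 = 84% with 56/112 = 50%. None of these counts is in the documents, and the figure requires that every first-meeting decliner be excluded. If decliners are counted, the bias is zero.
- **That assessment-only patients are counted as willing to exercise.** Section 3.1 uses the consent rate together with a rate for each option, and Table 1 lists program choices as a separate outcome. PPA patients can already be separated.

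It is also true that the required sample size is not understated on this account: the variance of a proportion is largest at 50%, so a different rate would not call for more patients.

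**Conclusion.** The point holds as a flaw in how the denominator is obtained. Followed as written, section 2.3 gives verified eligibility only for interested patients. Section 3.1 and Table 1 divide by eligible patients, and section 3.8 has all eligible patients in mind. These places need to be reconciled.

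Any bias is upward. Its size is unknown. At a true uptake of 50%, it exceeds the planned 5-point margin if more than about 18% of eligible refusers decline at the first meeting. That result rests on the plan's 50% and on those decliners being absent from the denominator, which is the consequence of the written steps and not something the plan declares.

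The assessment-only issue is a minor reporting point.

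**What to change.** 1. Before the first approach, apply the criteria that can be read from records (such as age, time on dialysis, hemoglobin, C-reactive protein, NYHA class and major amputation) to every patient in the unit. Do the same for new entrants at the three-monthly check. This should be done at the time, because laboratory values are hard to reconstruct later.
2. Define the primary Phase 1 rate as consenters over all record-eligible patients, including those who decline at the first meeting.
3. Report consent among screened-eligible patients as a secondary rate.
4. Add a sensitivity analysis for criteria not in the records, such as the Mini Mental score, by varying the assumed share of unscreened decliners who would have failed them.
5. As a reporting matter, give the share of eligible patients choosing an active program (U-PA, S-HB-LI or S-SU-LI) as willingness to exercise, separately from overall consent, which includes PPA. The option rates already planned supply it.

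**Cost.** A check of about 140 records and a reworded outcome definition. Reported uptake is likely to be lower. Some patients in the denominator would in truth be ineligible, which pulls the primary rate down. If the record check excludes no eligible patient, the primary and secondary rates bracket true uptake from below and above, which is the reason to report both.
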